| Research procedure | 
(1) Screening for inclusion (D-14) : After the subjects signed the informed consent, all pre-enrollment screening examinations were conducted in the periodontal/emergency comprehensive clinic of the research institution. Subjects who met the inclusion criteria and did not meet the exclusion criteria were selected Join the group. The investigator selected the subject's proposed treatment site (single tooth position/subject).
 
(2)Periodontal primary treatment (D-14~D1) : Periodontal primary treatment includes supragingival scaling, subgingival scaling and root treatment The surface is flat. Divided into 3 times, the specific treatment steps are as follows:
 
 
■ Supragingival cleaning (D- 14) : normal saline rinse and gargle, whole mouth ultrasonic supragingival cleaning and polishing, normal saline rinse;
 
■ Subgingival scaling (D-7±1, non-therapeutic dental area) : 2% bilan anesthesia, half-mouth ultrasonic subgingival scaling, flat root surface, polishing, normal saline rinse;
 
■ Subgingival scaling (D1, including treatment area) : 2% bilan anesthesia, the other half of the mouth ultrasound subgingival scaling, root surface flat, polishing, normal saline rinse.
 
 
(3) Local injection therapy (D1) : According to the randomly assigned number, all subjects were given bilateral multi-point local injection therapy of hDP-MSC cells/normal saline immediately after the peridental foundation treatment was completed. The local injection method for the peridental defect site is: Under local anesthesia, the periodontal probe was used to determine the top position of the alveolar ridge, and the needle was injected into the bottom of the periodontal bag (in the surrounding tissue at the bottom of the periodontal bag). After the needle reached the medial periodontal membrane of the alveolar ridge and touched the junction between the bone surface and the tooth root, the multi-point interstitial injection was performed on both sides of the buccal (lip) and lingual and palatine sides with a 1ml spiral syringe. The injection time is 20-30 seconds at each point. The stop point of the injection needle is located on the tooth root surface to ensure that the injected stem cell preparation can be in the tooth root The area is clustered. Specific operations are as follows:
 
 
■ DPSCs injection group: 48 subjects. Immediately after the completion of periodontal basic treatment, the patient was given bilateral multi-point injection at a single dental position, and the therapeutic dose was <math>1 \times 10^7</math> hDP-MSC cells (0.6mL suspension of normal saline)/dental position/person.
 
■ Saline iniecton group: 48 subjects. Immediately after the completion of periodontal basic treatment, the patient was given bilateral multi-point injection at a single dental position, and the therapeutic dose was 0.6mL normal saline/dental position/person.
 
 
Local stem cell secondary injection therapy (D30±3) : Only for secondary stem cells in the second phase of this study Subjects in the administration group. At the end of a one-month follow-up, the subjects were given more hDP-MSC cells on both sides Point local injection therapy. The local injection method of periodontal defect site is the same as the first local injection treatment:
 
 
■ Double DPSCs iniecton group: After 1 month follow-up, the subjects received bilateral multi-point injection at a single dental position and the therapeutic dose It was <math>1 \times 10^7</math> HDP-MSC cells (saline 0.6mL suspension)/dental position/person.
 
 
(4) Observation (D1) : After treatment, all subjects were admitted to the periodontal/emergency comprehensive clinic 2 Hours of adverse reactions observation and safety assessment.
 
(5) Follow-up (D7±1 telephone follow-up, D30±3, D90±3, D180±5, D360±5) :
 
 
■ Post-treatment follow-up: Subjects were followed up at D7±1 (telephone follow-up), D30±3, D90±3, and D180±5 once each after discharge, and clinical safety and efficacy indexes were collected.
 
■ Long-term follow-up: After the end of treatment, D360±5 follow-up was conducted once, clinical efficacy and immunological evaluation indicators were collected, and the study was ended.
 
 |

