| Effectiveness evaluation | 
① Primary efficacy measures
 
 
■ Oral clinical testing indicators: at screening periods, pre-treatment periods, and follow-up periods D90±3, D180±5, D360±5, examination was performed using a Florida probe, and the measurement of D90±3 was used as the evaluation endpoint.
 
■ attachment level AL (Periodontal depth PD + gingival recession GR).
 
 
② Secondary efficacy indicators
 
 
■ Imaging test indicators: at screening periods and follow-up periods D90±3, D180±5, and D360±5, examinations was performed using a Florida probe, and the screening periods was used as baseline, D180±5 measured value was used as the evaluation endpoint.
 
• Changes in periodontal defect height at 3, 6, and 12 months after the end of treatment compared with baseline (CBCT measurements, change of periodontal defect height = difference in distance from the cemento-enamel to the top of the alveolar ridge).
 
• Changes in mean alveolar ridge density at 3, 6, and 12 months after the end of treatment compared to baseline (CBCT measurements).
 
■ Oral clinical testing index: at screening periods and follow-up periods D90±3, D180±5, D360±5, using Florida probe for examination, use the measurement of D90±3 as the evaluation endpoint.
 
• PD compared to baseline;
 
• Periodontal healing compared to baseline (probing bleeding index BOP, gingival recession GR, tooth mobility TM).
 
 |

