**【Adverse Event Record】**

**【Record of combined medications/treatments】**

**【Double DPSCs Injection Treatment】** : only for subjects in the double DPSCs injection group in Phase II of this study. At the end of the one-month follow-up visit, subjects received a bilateral multi-point inject hDP-MSC. Periodontal defect sites were injected in the same manner as the first local injection treatment.

■ Double DPSCs injection group: at the end of the one-month follow-up visit, the subjects were given bilateral multipoint injections into individual tooth sites at a single treatment dose of about  $1 \times 10^7$  hDP-MSC (saline 0.6mL suspension) / tooth / person.

The investigators recorded the start and end time of the subjects' local injection treatments.

**【Vital Signs】** :only for subjects in the Phase II double DPSCs injection group of this study. 2h±30min after the end of local injection treatment, record: respiration, heart rate, blood pressure (systolic and diastolic), temperature (axillary), and clinical assessment of general condition.

**【Laboratory tests】** :Only for subjects in the Phase II S double DPSCs injection group of this study. After the local injection treatment 2h±30min after the end of local injection treatment.

☞Inflammation indicator: Ultrasensitive C-reactive protein.

☞Immunologic tests: IgA, IgG, IgM, total IgE.

**【Adverse event record】** : Only for subjects in the Phase II Stem Cell Secondary Dosing Group of this study, who were observed 2 hours after treatment before left the hospital and adverse events were record.

(5) **Post-treatment follow-up 3:** 3 months (D90±3 days) after the end of treatment.

**【Periodontal Clinical Indicators】** : Periodontal examination was standardized using the Florida Probe of the Beijing Stomatological Hospital, Capital Medical University. Records: periodontal attachment level AL, periodontal probing depth PD, probing bleeding index BOP, gingival recession GR, tooth mobility TM, and the proposed treatment site (single tooth/subject) were selected by the investigator.

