**In the second phase, there are 3 groups, and the therapeutic dose of stem cell preparation is as follows:**

■ **Normal saline control group:** The therapeutic dose was 0.6 mL/tooth position, and normal saline 0.6 mL/tooth position/person.

■ **Stem cell therapy group:** The therapeutic dose was 0.6 mL/tooth position, the cell volume was about  $1 \times 10^7$  hDP-MSC cells/tooth position/person, and the suspension was Normal saline 0.6 mL.

■ **Stem cell secondary administration group:** The first treatment dose was 0.6 mL/tooth position, and the cell volume was about  $1 \times 10^7$  hDP-MSC cells/tooth position/person. The suspension was 0.6 mL of normal saline. One month later, the second treatment dose was the same as the first treatment dose of 0.6 mL/tooth position, the cell volume was about  $1 \times 10^7$  hDP-MSC cells/tooth position/person, and the suspension was 0.6 mL of normal saline

**3. Stem cell preparation treatment:** local bilateral multi-point injection of a single affected tooth of the subject.

(1) **Treatment operation procedures:** under local anesthesia, use a periodontal probe to determine the position of the alveolar ridge, insert the needle at the bottom of the periodontal pocket (in the tissue around the bottom of the periodontal pocket), and wait for the needle to reach the periodontal ligament on the medial side of the alveolar ridge, and touch the junction between the bone surface and the tooth root, and use 1ml screw. The rotary syringe is injected at multiple intervals on both sides of the buccal (lip) and tongue and palate, and each injection time is 20-30 seconds. The insertion point of the needle is located on the surface of the tooth root to ensure that the injected drug can accumulate at the tooth root. After the end of the treatment with bilateral multi-point local injection of hDP-MSC cells/normal saline, all subjects underwent 2-hour adverse reaction observation and safety evaluation in the periodontology/emergency comprehensive care center.

(2) **Course of treatment:** In the first phase of this study, one local injection administration is a course of treatment. In the second phase of this study, two local injections were administered as a course of treatment, and subjects in the stem cell secondary administration group were administered with one local injection one month after the first dose.

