## 2. Efficacy evaluation index

### (1) Primary efficacy measures

- **【Oral clinical testing indicators】** During the screening period, before administration, and follow-up period, D90±3, D180±5, and D360±5 were examined with Florida probe, and the measured value of D90±3 was used as the evaluation endpoint.  
Periodontal attachment level AL (PD+GR).

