## **(XX) Follow up plan and implementation methods**

The follow-up period of this study was 12 months, with telephone follow-up at  $D7 \pm 1$  after local injection treatment and regular follow-up at  $D30 \pm 3$ ,  $D90 \pm 3$ ,  $D180 \pm 5$ , and  $D360 \pm 5$ . The investigator should observe the subjects strictly according to the protocol, and the subjects should try to follow up regularly as requested by the investigator. During the study period, treatment and follow-up should be performed in strict accordance with the protocol, taking into account the fact that a time window of  $\pm 3$  days is allowed from 1 month after treatment with the stem cell preparation, and a time window of  $\pm 5$  days is allowed from 6 months after treatment. If a subject exceeds the window at a follow-up visit, the next follow-up visit should be recalculated based on the time of the previous visit.

The examinations required to be performed at each follow-up visit were conducted by the investigator, and the relevant examinations were conducted in the imaging department, laboratory department and other specialized departments of the research center, and timely, accurate and complete records were made of the clinical indicators, laboratory results and imaging results of each observation, and of the combination of medications, adverse events, and so on. For subjects with adverse reactions, all indicators of the screening period were followed up until they were normalized.

**1. Post-treatment follow-up 1:** Telephone follow-up 1 week ( $D7 \pm 1$  day) after the end of treatment.

- a. Record of adverse events
- b. Record of co-administration of drugs/treatment

**2. Post-treatment follow-up 2:** 1 month ( $D30 \pm 3$  days) after the end of treatment.

a. Vital signs: respiration, heart rate, blood pressure (systolic, diastolic), temperature (axillary), clinical assessment of the general body condition, and another checkup  $2h \pm 30min$  after the end of the second administration of treatment for the subjects in the secondary stem cell administration group in the second phase of this study.

b. Laboratory tests:

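### The primary D90 attachment-level measurement is not guaranteed to fall at the same time since the D1 scaling: a late visit re-times the next one without limit, and the D90 anchor is ambiguous in the double-injection arm

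*Protocol*

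**What the plan says.** **Primary endpoint.** Section (15), item 2(1), names AL as the primary measure and states that "the measured value of D90±3 was used as the evaluation endpoint". The effectiveness row of the scenario summary says the same.

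**Time zero.** The research procedure in the scenario summary puts scaling of the treated area on D1 ("Subgingival scaling (D1, including treatment area"), with the first injection immediately afterwards.

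**Visit series.** The same row states: "Subjects were followed up at D7±1 (telephone follow-up), D30±3, D90±3, and D180±5 once each after discharge". The study schedule table gives all arms a single D90±3 column. The extra injection of the double-injection arm sits on the same day count: "Local stem cell secondary injection therapy (D30±3").

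**Visit headings.** Section (V), item 4(5), times the D90 visit as "3 months (D90±3 days) after the end of treatment", and section (XX), item 3, uses the same anchor. The 6- and 12-month headings follow the pattern, as do the CBCT secondary measures: "Changes in periodontal defect height at 3, 6, and 12 months after the end of treatment compared with baseline".

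**Course of treatment.** Section (12), item 3(2), says: "In the second phase of this study, two local injections were administered as a course of treatment".

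**Out-of-window visits.** The opening paragraph of section (XX) says that if a subject exceeds the window at a visit, "the next follow-up visit should be recalculated based on the time of the previous visit". It gives no maximum shift and no instruction to return to the D1-based dates.

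**The concern.** All subjects have the treated area scaled on D1, and AL may change with time since scaling whether or not cells are given. In the earlier data summarised in section (III), probing depth improved in both groups. A comparison of arms at D90 is cleanest when every subject is probed at the same time since D1.

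Two features of the text work against that. The recalculation rule lets the primary visit slide for any subject whose preceding visit was late, and the shifted date is then the date the protocol itself prescribes. The end-of-treatment wording has one meaning where treatment ends on D1 and possibly another where a second injection is given about a month later. If site staff took the second meaning in the double-injection arm only, time since scaling would be confounded with treatment in an arm of 30 of the 96 planned subjects.

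**Working it through.** **Inputs**
- Scaling of the treated tooth and first injection: D1 (scenario summary, research procedure).
- One-month visit and second injection: D30±3, i.e. D27-D33 (same place; schedule table).
- Primary visit: D90±3, i.e. D87-D93 (section (15); schedule table).
- Planned interval between these visits: 90 − 30 = 60 days. That the recalculation keeps this interval is an assumption; section (XX) does not say how the new date is computed.

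**1. The plan as scheduled, all visits counted from D1**
- Time since scaling at the primary visit: 90 − 1 = 89 days (range 87 − 1 = 86 to 93 − 1 = 92), the same in every arm.
- Double-injection arm, time since second injection: 90 − 30 = 60 days (range 87 − 33 = 54 to 93 − 27 = 66).

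**2. Effect of the recalculation rule**

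New primary target = actual day of the one-month visit + 60, with ±3 days around it.

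| One-month visit held on | Primary target | Window | Target beyond D93 by |
|---|---|---|---|
| D34 | D94 | D91-D97 | 1 day |
| D40 | D100 | D97-D103 | 7 days |
| D44 | D104 | D101-D107 | 11 days |
| D60 | D120 | D117-D123 | 27 days |

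D34 is the first day outside the one-month window, and it already moves the target past D93. From D37 the new window (94 to 100) no longer overlaps D87-D93 at all. Under the rule, each day of delay in the one-month visit moves the primary probing by one day.

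**3. The two readings of the D90 visit in the double-injection arm**
- Counted from D1: D90 (D87-D93), as in step 1.
- Counted from the second injection: 30 + 90 = D120, range 27 + 87 = D114 to 33 + 93 = D126.
- Difference from the other arms on the second reading: 120 − 90 = 30 days nominal; extremes 114 − 93 = 21 and 126 − 87 = 39 days.

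**4. Which reading does the text support?**
- For the later date: the heading of the D90 visit, taken with section (12), under which two injections form the course of treatment in the second phase.
- For D1: the primary endpoint is defined only as D90±3. The schedule has one D90 column for all arms. The second injection is itself placed at D30±3 on that clock. The one-week and one-month visits are also headed as timed from the end of treatment, and the second injection is given at the end of the one-month visit, so in those headings the phrase can only mean the D1 injection.

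The D1 reading is the better supported. The wording still leaves the other open, because the same phrase cannot be read literally in both section (12) and the one-month heading for the double-injection arm.

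**5. A side point on time zero.** Section (V), item 4(2), labels the cleaning of the treated area D-1, although that block is headed D1 and the scenario summary has D1. These passages should be reconciled.

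**The case against.** The strongest reply is that the primary endpoint has one definition, D90±3, and that the end-of-treatment phrase in the CBCT text concerns secondary measures. Applying the later anchor consistently would also require a telephone call at about D37 and a one-month visit at about D60 in the double-injection arm, and neither exists. This largely stands. A reader might infer that the double-injection arm is measured 30 days, or a third, later than the others; the documents do not establish that.

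On the recalculation rule, the reply is that it treats all arms alike, that failure to attend on time is a withdrawal criterion, and that the per-protocol set requires compliance. The first point stands: the rule alone produces scatter and not a systematic difference. The other two help less, because a re-timed visit is what the protocol instructs, and nothing says how it is classified for analysis. For the same reason one cannot claim that such a visit counts as in window.

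Three further inferences go beyond the text:
- **Longer delays in the double-injection arm because product must be ordered.** Section (13) asks for one day's notice, which fits within a ±3-day window.
- **Extra time favouring that arm.** No AL course between D90 and D120 is given, and in the earlier data 2 of 5 saline subjects had redness, swelling and bleeding at day 90.
- **Every later visit shifting.** The rule speaks of the next visit; carrying the shift on to D180 and D360 is plausible but not stated.

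**Conclusion.** The point holds in a limited form: measurement of the primary endpoint at a common time since the D1 scaling is not guaranteed.

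The firm part is the recalculation rule. It is explicit, has no cap, and can take a subject's primary probing outside D87-D93 while the plan is being followed. The size depends on the delay: about D100 for a one-month visit on D40, assuming the 60-day interval is preserved. The consequence is unequal timing between subjects in any arm.

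The second part is an ambiguity. The D90 visit of the double-injection arm could be read as due at about D120 (D114-D126), but the schedule and the one-month heading favour D1. On that reading the nominal time since scaling is equal in all arms, and the double-injection arm is measured about 60 days after its second injection.

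The effect on AL of either kind of timing difference cannot be computed, because the protocol gives no figures for AL over time. The 33% that one can form from 30/90 is elapsed time and not a measure of bias.

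**What to change.** 1. State once that the outcome assessments at D90, D180 and D360 are counted from D1 in every arm.
2. Align the end-of-treatment wording with this in the effectiveness row of the scenario summary, section (V) items 4(5) to 4(7), section (15) item 2(2), and the visit headings of section (XX).
3. Replace the recalculation rule, for outcome assessments, with: a late visit does not change later target dates; the actual day is recorded; late values stay in the full analysis set. The last clause matters because AL is not probed between D1 and D90. If a late value were set aside as missing, the planned last-observation-carried-forward rule would carry a pre-treatment value into the primary analysis.
4. Report that D90 in the double-injection arm falls about 60 days after its second injection.
5. If any visits were already re-timed, or held near D120, report the actual days by arm and add a sensitivity analysis by actual assessment day.

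This is a clarifying amendment to assessment timing and adds no visits. Its one drawback is that a subject whose second injection is late has a shorter interval from that injection to D90: with an injection on D40, 90 − 40 = 50 days instead of 60. Recording actual days makes this visible.

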## **6. Unplanned follow-up and treatment**

If an adverse event occurs during the study period, the investigator may increase the number of follow-up visits or treatments, i.e., unplanned follow-up visits and treatments, according to actual needs. The investigator must accurately record the contents of each unplanned follow-up visit and treatment in the unplanned follow-up section of the original medical record and CRF.

- Chief complaint symptoms;
- Vital signs: respiration, heart rate, blood pressure (systolic, diastolic), temperature (axillary), clinical assessment of general condition;
- Intraoral photography: postoperative condition of the oral cavity and each injection site;
- Laboratory tests: relevant laboratory tests for the screening period as practically required;
- Adverse event records;
- Records of combined medications/treatments;
- Decision on whether to perform imaging tests (CBCT examination) and the selection of appropriate ancillary screening programs, as actually required;
- Appointment for the next follow-up visit.

## **6. Follow-up of withdrawn/dislodged subjects:**

Subjects may withdraw from the study at any time during the study. The researcher will examine all subjects to determine their periodontal health status, inform them of the precautions to be taken, and to contact the researcher promptly after any discomfort occurs. The researcher should also leave the contact information of the subjects to facilitate follow-up visits if necessary. In case of early withdrawal/exfoliation, the subject should contact the investigator or return to the hospital if any discomfort occurs during his/her absence.

For subjects who withdraw/dislodge early, the investigator should try to find out why they withdrew/dislodged and accurately record the time of withdrawal from the study/ shedding time.

